### Recruitment

In order to facilitate recruitment, a logo was designed for the DAILY study, which has a high recognition value for the test persons and underlines the official character of the study (Figure 2). After screening for eligibility, participants are recruited during their clinical stay at either the specialist ward or the outpatient clinic for addiction disorders. A member of the study staff addresses the candidates personally and finds out whether there is in principle interest in participating in a concomitant therapy study for AUD patients. Candidates are given at least 1 day to consider. In the event of positive feedback, they are allocated to either the intervention or control group.

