**Figure 1 F1:**
[figure not shown]
Procedure of the DAILY study. Patients are screened and recruited by a member of the study staff. After 1 day at the earliest the participants sign the consent form. On this day, they are informed about the contents of the study; the contents discussed differ between intervention and control group. In addition, questionnaires are filled out and blood is drawn. During the week, a psychoeducation session takes place in which the contents and the aims of the study are deepened, further questionnaires (Table 1) are filled in, and a test diary is handed out to record times of daily actions which act as *Zeitgebers*. After at least 1 week, the diary is evaluated and a daily structure plan for regular exposure to *Zeitgebers* is worked out together with the test persons, to which they should adhere for the next 4 weeks. Subjects in the control group are not given instructions on how to structure their daily routine but are still asked to complete the diary. At least one telephone appointment is made for the time the subjects fill out the diaries to maintain compliance. After 4 weeks, there will be a final personal appointment where the diaries will be collected, all questionnaires will be repeated, and blood will be drawn again.

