### Informed Consent and Baseline Assessments

To participate in the study, all participants need to sign an informed consent in the 1st week (Figure 1). Afterwards, irrespective of the group allocation, a semi-structured interview is conducted to assess demographical data: age, gender, employment status, occupation, and marital status. Medical data are evaluated as well: size, bodyweight, blood pressure, current medications, and information about previous alcohol problems and possible depressive episodes. In addition, the questionnaires described below (Table 1) are filled out together with the participants. Lastly, blood samples are collected. This appointment is also used to prepare the test persons for the topics and contents of their respective groups.

**Table 1 T1:** Overview of questionnaires, physiological assessments, and time points.

**Assessment category**	**Assessment instruments**	**First session**	**Last session**	**Between sessions**
Baseline	Demographics	x		
Circadian	Sleep-Food-Diary			x
	Munich ChronoType Questionnaire (MCTQ)	x	x	
	Pittsburgh Sleep Quality Index (PSQI)	x	x	
Alcohol use	Alcohol use disorders identification test (AUDIT)	x	x	
	European Addiction Severity Index (EuropASI)	x	x	
	Timeline Followback 30 (TLFB)	x	x	
Depression	Hamilton Depression Scale (HAMD)	x	x	
	Inventory of Depressive Symptomatology (IDS-SR)	x	x	
Self-efficacy	Self-Efficacy Questionnaire (SWE)	x	x	
Blood values	Blood draws	x	x	

The further course of the study and the contents of the following appointments are described separately for the intervention group and the control group.

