### Intervention Group

#### Week 1: Psychoeducation and Test Diary

After baseline assessments, a few days later in the same week, the test persons participate in individual 1-h psychoeducation sessions about circadian clocks and their effects on health and psychiatric disorders, such as addiction and depression. The scientific content is communicated in simple language. Firstly, the participants get explained that circadian rhythms can be found virtually everywhere in nature and that they have impact on essentially all physiological processes, including sleep-wake cycles, hunger, digestion, wound healing, cellular functions, and molecular processes. A focus is on their involvement in neurobiological systems, such as reward, addiction networks, and behaviors. During the session, the test subjects are led to understand how important regular daily routines are for mental and physical health. Therefore, the study assistant emphasizes the importance of certain environmental cues that can serve as *Zeitgebers*, such as light and food. Together with the participants, the impact of light on sleep is discussed and how light can be avoided at late hours (e.g., by stopping the use of mobile phones, watching TV, or playing computer games after sunset or by using blue-light filters). Furthermore, the importance of regular mealtimes is discussed as food is an important *Zeitgeber* for many organs, including brain areas involved in the development of addiction. At the end of this session, the study assistant hands out a circadian diary (Supplementary Table 1), which the participant is asked to fill out for 1 week. With the help of the diary, data on times of meals, snacks, activity times, sleep duration, sleep quality, mood, and alcohol craving are collected on a daily basis. At this point in time, the test persons do not yet receive any concrete instructions as to when they should execute activities. Rather, they are instructed to use the following days to see if they can recognize certain temporal patterns in their own behavior and to consciously follow these patterns. Filling out the test diary serves on the one hand to create an awareness of their own daily rhythms. Besides, it gives the test persons the opportunity to familiarize themselves with the filling out of the diary. On the other hand, the data obtained on eating and sleeping times can be used in the next session as a basis for drafting a daily structure plan.

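### Allocation precedes baseline, and baseline shares a visit with arm-specific content, so start values and entry to the analysis set can depend on the arm

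*Protocol article*

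**What the plan says.** All references are to the protocol article.

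- **Recruitment.** Staff first establish interest in principle. Then "Candidates are given at least 1 day to consider", and "In the event of positive feedback, they are allocated to either the intervention or control group".
- **Consent.** The Figure 1 legend says "After 1 day at the earliest the participants sign the consent form". The section Informed Consent and Baseline Assessments says "all participants need to sign an informed consent in the 1st week". It then describes the interview (the same whatever the allocation), questionnaires completed jointly with the participant, and blood samples.
- **Arm content on the same day.** The Figure 1 legend says of the consent day: "On this day, they are informed about the contents of the study; the contents discussed differ between intervention and control group". The baseline section agrees: "This appointment is also used to prepare the test persons for the topics and contents of their respective groups".
- **Psychoeducation session.** The legend describes a later session that week: "a psychoeducation session takes place in which the contents and the aims of the study are deepened, further questionnaires (Table 1) are filled in". The Week 1 section instead places this session a few days after the baseline assessments.
- **Test diary.** It is handed out at the end of the DAILY psychoeducation session. DAILY participants are asked to see whether they can "recognize certain temporal patterns in their own behavior and to consciously follow these patterns". The Control Group section says that controls are asked only to complete the diary carefully.
- **Blinding.** Under Allocation, participants are not told their arm until the study ends. Study staff may decode it.
- **Analysis set.** Data Analysis defines intention-to-treat as those who completed the first-session questionnaires and the first diary week. People who withdraw consent and have no baseline measurements count as dropouts.

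**The concern.** A baseline value is safe to subtract only if the arm could not have influenced it. Here the arm is already assigned when baseline is taken, the staff may know it, and the same appointment introduces arm-specific topics. The Hamilton scale is observer-rated and the self-reports are filled in with assistance, so both leave room for influence. Any arm-related shift passes into every change from baseline.

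The second issue is who gets analysed. If people leave between allocation and the end of diary week 1, and do so differently by arm, the analysed groups are no longer the randomised groups. The label intention-to-treat would not then give its usual protection.

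The third is the Routine Variability Score, a primary outcome. Its earliest measurement in the DAILY arm comes after teaching designed to change it.

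**Working it through.** The article states no sample size, refusal rate, effect size or power, so there is no figure to reproduce. The check sets the passages in sequence and asks which analyses are exposed.

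**1. Order of events.**
- Recruitment: interest in principle, at least 1 day to consider, positive feedback, allocation.
- Informed Consent and Baseline Assessments, and Figure 1: signature, interview, questionnaires, blood and introduction to arm topics, all at one 1st-week appointment.
- Week 1: psychoeducation a few days later, then the test diary.

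Allocation before baseline is clear: the baseline section refers to the allocation as existing, and the content discussed that day already differs by arm. Allocation before the signature is the plain reading of the same passages, but no sentence says so outright.

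**2. Order within the appointment.** Neither passage says whether arm content comes before or after the questionnaires, so nothing stated protects the baseline from it.

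**3. Conflict on questionnaire timing.** The Figure 1 legend puts further Table 1 questionnaires in the psychoeducation session. The Week 1 section has the baseline assessments finished before that session. Both cannot hold for the same questionnaires.

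**4. Effect on each planned comparison.** Let *b* be the arm-related shift in the measured baseline of the DAILY arm relative to control.
- Endpoint contrast = (DAILY end) − (control end). Baseline does not enter, so the bias from *b* is 0.
- Change contrast = (DAILY end − DAILY start) − (control end − control start). The start term carries *b*, so the bias is −*b*.

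The start-to-end analysis, listed second in Data Analysis, carries the whole shift. The unpaired endpoint comparison, listed first, carries none. No passage gives a value for *b*.

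**5. Entry to the analysis set.** Both entry conditions, first-session questionnaires and diary week 1, are met after allocation, and the diary week is completed after arm content has begun. Study Hypotheses and Objectives expects the added psychoeducation to help participants complete therapy and stay compliant. The plan's own theory thus allows diary completion to differ by arm. This exposes the endpoint comparison as well as the change analysis.

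**6. Diary week 1 as a start value.** Table 1 lists the diary only between sessions, so the test week is the earliest score available. In the DAILY arm it follows teaching on regular routines and the instruction to follow one's own patterns. If that teaching improves regularity, DAILY starts lower on variability than it would untreated. The measured fall is then too small, and the change contrast is probably biased towards zero.

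**The case against.** The strongest defence has five parts.

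- **Consent.** A reader might infer that the article openly randomises before written consent. It does not say so. Positive feedback and signature both come after at least 1 day and could fall at one contact. This stands: the point is firm for baseline and an inference for consent.
- **Visit order.** The baseline section mentions group topics last, and a condensed article may leave the sequence to the full protocol. This stands in part. The silence alone would be no finding, but sharing one appointment and the conflict between the Figure 1 legend and the Week 1 section are both in the text.
- **Diary week 1.** It is called a test diary, serving awareness, practice and drafting the plan. No passage names it as the start value for the Routine Variability Score. This stands: the bias towards zero arises only if it is used that way. Its role as an entry condition, however, is explicit.
- **Mitigation.** Participants are not told their arm, both arms have the same number of sessions, and blood values are hardly open to assessor influence. This narrows the measurement concern mainly to the Hamilton scale and the assisted self-reports. It does not blind the staff.
- **Pilot status.** The Design section disclaims a primary focus on proving treatment success. That lowers the stakes, but Data Analysis still plans significance tests between arms, and a pilot meant to inform a main trial should not hand on this order.

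**Conclusion.** The concern holds as a weakness of sequence. Start-to-end changes can depend on the arm through baseline. All between-arm comparisons, including the endpoint one, can depend on it through entry to the analysis set. Diary week 1 is not an untreated value for a primary outcome.

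Two stronger conclusions are not supported. A reader might infer that every between-arm result is distorted by a shifted baseline, but the endpoint comparison is free of that bias. A reader might also want the bias expressed in standard deviations or in patients lost. That would need a baseline shift and a refusal rate, and the article gives neither, so the size stays undetermined.

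The conclusion assumes that the staff taking baseline know, or can find out, the arm. The Allocation section permits this, and the arm-specific content of the visit implies it. The correction is worth making because it is cheap, not because bias has been shown.

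**What to change.** 1. Obtain written consent and complete the interview, all baseline questionnaires and the blood draw before the next allocation is opened. Give arm-specific content only after that.
2. Keep baseline questionnaires out of the psychoeducation session, and reconcile the Figure 1 legend with the baseline and Week 1 sections.
3. Remove diary week 1 as a condition for the intention-to-treat set, and analyse everyone randomised. With baseline completed first, each of them has data from which the planned imputation can start.
4. Do not use diary week 1 as a baseline. Compare the arms on the Routine Variability Score in weeks 3–6 only.

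Handing out the diary at consent is optional. It yields only a few days before psychoeducation, whereas Measured Outcomes scores the variability over 1 week, so it would not give a comparable baseline.

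Cost: the list is opened a few days later, and there is no change-from-baseline analysis for the Routine Variability Score. No extra visit or staff is needed, because psychoeducation is already planned a few days after baseline.

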### Eligibility Criteria

All persons are considered eligible on whom the below exclusion criteria do not apply. Subjects are only included in the study if they can assess the nature and scope of the investigations. Written consent is required for inclusion. The study is conducted in accordance with the principles of the Declaration of Helsinki with its amendments of Tokyo, 1975, Hong Kong, 1989, Somerset West, 1996, Seoul, 2008, and Fortaleza, 2013. The subjects must fulfill diagnostic criteria for AUD according to ICD-10 F10.2 and be of age 18–75 years. Smokers are eligible for this study. In case of dependency on other substances, the subjects must have been abstinent from these substances for at least 12 months at the time of study enrollment. One outcome of this study is the change in depressive symptoms in the subjects. For this reason, AUD patients with concomitant diagnosed MDD as well as substance-induced depression are included. However, a diagnosed depression is not a prerequisite for inclusion in the study.

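### The arm is already set at the appointment where consent is signed and baseline is measured, so staff-rated and staff-assisted baseline values can be influenced by it

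*Protocol article*

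**What the plan says.** All references are to the protocol article.

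- **Recruitment.** A staff member "finds out whether there is in principle interest in participating in a concomitant therapy study for AUD patients". Candidates have a minimum of one day to think it over. Then: "In the event of positive feedback, they are allocated to either the intervention or control group".
- **Allocation.** Assignment comes from a computer-generated list. Study staff may decode the study code; patients are not told their arm until the study ends.
- **Eligibility Criteria.** "Written consent is required for inclusion".
- **Informed Consent and Baseline Assessments.** Consent is signed in week 1. Next: "Afterwards, irrespective of the group allocation, a semi-structured interview is conducted to assess demographical data". Questionnaires are completed jointly with the patient, and blood is taken last. The section adds: "This appointment is also used to prepare the test persons for the topics and contents of their respective groups".
- **Figure 1 caption**, on the day of signature: "On this day, they are informed about the contents of the study; the contents discussed differ between intervention and control group". Later in that week, "a psychoeducation session takes place in which the contents and the aims of the study are deepened, further questionnaires (Table 1) are filled in".
- **Intervention Group, Week 1.** The first diary is handed out at the end of the arm-specific psychoeducation session.
- **Data Analysis.** The analysis set consists of those who completed the first-session questionnaires and the first diary week. Groups are compared at the endpoint, and separately on change from start to end.

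**The concern.** A baseline value is protected from the treatment comparison only if it is recorded before anyone can act on the allocation. Here patient and staff meet for baseline with the arm already drawn, and the same meeting introduces that arm's topics. A rating or a jointly completed questionnaire can then drift in one arm, through the rater's knowledge or the patient's preparation. An analysis of change would read that drift as a treatment effect.

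A second question is who gets analysed. If completing the first session and the first diary week both follow allocation, they are post-randomisation events, and the groups analysed need not be the groups randomised.

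**Working it through.** The article gives no sample size, loss rate or baseline variance to reproduce, so the check is mainly on the order of steps.

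**1. Is the arm set by the baseline appointment?** Yes, and this does not depend on the order of headings. The Figure 1 caption says that content differs by arm on the consent day. The baseline section says that the appointment with questionnaires and blood prepares patients for their own group's topics. Neither is possible unless the arm is known that day.

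**2. Does arm content come before the questionnaires within that day?** Not settled. The caption mentions the arm-specific information first and the questionnaires after it. The baseline section lists interview, questionnaires and blood, and mentions preparation last. The caption also places some Table 1 questionnaires in the week of the psychoeducation session, whereas Table 1 assigns all repeated questionnaires to the first session.

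**3. Which measures are exposed?** Most exposed is the HAMD, an external rating and a secondary outcome. The questionnaires completed jointly with staff, including the drinking measures that serve the primary outcome, are exposed to a lesser degree. Recall of the past 30 days leaves less room for drift. Age, gender and blood values are little affected.

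**4. Which analysis carries the shift?** Let D be the between-arm difference at the endpoint and b an artificial shift in one arm's baseline.

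- Endpoint comparison: D. The shift b does not appear where endpoints are observed. An indirect route exists only if missing endpoints are imputed from baseline data.
- Change comparison: D − b. The whole shift appears.
- Baseline-adjusted comparison with slope 0.5 (assumed, for reference): D − 0.5b.

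With b = 1 HAMD point and SD 5 to 6, both assumed:

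- Change: 1/6 = 0.17 to 1/5 = 0.20 SD.
- Adjusted: 0.5 × 1/6 = 0.08 to 0.5 × 1/5 = 0.10 SD.

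The sign depends on which arm shifts and in which direction.

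**5. Does allocation precede the signature?** It appears to. The stated trigger is positive feedback rather than a signature, and consent is described after recruitment and allocation. However, the caption gives the same interval of at least one day before signing that Recruitment gives for considering, so feedback, signature and allocation could fall on one day.

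**6. Who is analysed?** Both conditions for the analysis set are met only after the arm is set. If baseline moved ahead of allocation, the questionnaire condition would become harmless. The diary condition would not, because that diary starts after the arm-specific session. Data Analysis also ends by saying that everyone other than those who withdraw consent without baseline is analysed under ITT. A patient with baseline but an incomplete first diary week is thus left out by one sentence and kept by another.

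**The case against.** The strongest reply is that this is a condensed article on a pilot that does not mainly aim to prove efficacy. Patients are not told their arm, both arms receive the same number of sessions and the same attention, and the endpoint comparison between arms needs no baseline value. These points limit the harm. They do not remove it, because the article itself describes arm-specific content at the baseline appointment and plans a start-to-end comparison.

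A reader might go further and infer three things that the document does not support.

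- *Patients are randomised on a verbal yes before signing.* The article does not say the feedback is verbal, written consent is required for inclusion, and the steps could coincide.
- *Allocated patients who never sign are discarded as dropouts.* The dropout rule concerns people who withdraw consent, which presupposes that they gave it. Dropout frequency is also compared between arms. No stated rule covers people who never sign, and without a refusal rate the number affected cannot be worked out.
- *Loss differs by arm.* This is possible, since staff may know the arm and content differs on the consent day, but nothing shows it. Blinding of patients makes it less likely.

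**Conclusion.** The concern holds for the order of allocation and baseline. As written, the arm is set before or at the baseline appointment, so staff-rated and staff-assisted baseline values are open to influence, and any shift passes in full into the start-to-end comparison. Its real size is unknown; the 0.17 to 0.20 SD per HAMD point rests on an assumed shift and an assumed SD.

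For consent, the supported conclusion is narrower: Eligibility Criteria, Recruitment, and Informed Consent and Baseline Assessments should be reconciled, because together they suggest allocation before signature without stating it. The first-diary-week condition is a separate weakness in the analysis set, and reordering the visit would not cure it.

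This should be corrected, more so because the pilot is meant to inform a main trial that could inherit the same enrolment order.

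**What to change.** For patients not yet enrolled, state one order in Recruitment, Allocation, Informed Consent and Baseline Assessments, and Figure 1:

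1. written consent;
2. interview, all first-session questionnaires and blood;
3. draw of the next entry on the randomisation list;
4. arm-specific preparation.

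Bring the Figure 1 caption into line with Table 1, so that no baseline questionnaire is left to the week of psychoeducation.

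In Data Analysis, define the analysis set as all randomised patients by allocated arm, and drop the condition of a completed first diary week. Report every allocated patient by arm, including any who were allocated but did not sign.

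The cost is a short procedural amendment. The steps already exist, so no extra visit, staff or patients are needed. The Limitations section says that the study is under way, so patients already enrolled remain under the old order, and the report should say so.
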